## Data Collection and Management

### Monitoring

#### *Adverse events and adverse reactions*

The use of intrathecal drug delivery (IDD) systems does have inherent risks. This study aims to perform IDD refills at home instead of at the hospital. Nevertheless, from a technical point of view, the performance of IDD refills at home carries the same risk as performing them in a hospital setting.

### Definitions and reporting

An adverse event is defined as an unexpected medical occurrence in a participant after exposure to a medicine or treatment, which is not necessarily caused by that medicine or treatment. An AE can therefore be any unfavorable and unintended sign (including an abnormal laboratory finding), symptom or disease temporally associated with the use of a product, whether or not considered related to the product. Any worsening (i.e., any clinically significant adverse change in the frequency or intensity of a pre-existing condition) should be considered an AE.

Adverse reactions are defined as all untoward and unintended responses to medicinal products related to any dose administered.

### Reporting period

An AE possibly related to the refill and the total number of AEs will be systematically reported from baseline until the end of the study.

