| Data to be collected:       | 
 
- Patient comfort – General Comfort Questionnaire (GCQ)
 
- Quality of Life (QoL) – McGill Quality of Life Questionnaire (MQOL) and EuroQol (EQ-5D-5L)
 
- Pain intensity – Visual Analogue Scale (VAS)
 
- Pain interference – Patient-Reported Outcomes Measurement Information System
 
- Stress – saliva samples with synthetic salivettes (Sarstedt AG & Co., Nümbrecht, Germany)
 
- Patient anxiety – State Trait Anxiety Inventory (STAI)
 
- Self-efficacy – General Self-Efficacy (GSE) Scale
 
- Caregiver burden – Zarit Burden Interview (ZBI)
 
- Patient satisfaction – Seven-point Likert-scale
 
- Tele-monitoring quality
 
- Time of the refill
 
- Safety
 
- Health expenditure
 
- Patient preference
 
 |
| Endpoints:                  | 
The primary endpoint is to observe whether there is a difference in the scoring of the General Comfort Questionnaire between patients with chronic non-cancer pain or spasticity after receiving a pump refill at home versus in the hospital. Each patient will receive two pump refills at home and two in the hospital.
 
The secondary outcome is whether the two arms differ on quality of life (QoL), pain intensity, pain interference, stress, anxiety, self-efficacy, burden of caregivers for patients who receive IDD, patient satisfaction, consultation time, safety, health expenditure, and patient preference. A mixed model analysis will be used with timepoints at baseline and after each refill.
                                                                                                                              |

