### Secondary Objectives

The secondary objective is to evaluate if there is a difference in health-related quality of life, pain intensity, pain interference, stress, anxiety, general self-efficacy, burden among caregivers, patient preference for the location of the refill and in number of (serious) adverse events (e.g., infection, overdose). The third objective is to conduct an economic evaluation of intrathecal pump refills at home versus at the hospital, based on healthcare expenditure and (in)direct costs.

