### Safety

Patients will evaluate the overall safety of the procedure using a seven-point Likert scale. In addition, both the researchers (at home and at the hospital) will assess safety on three levels: (1) overall perceived safety of the procedure using a seven-point Likert scale; (2) environmental safety, assessed through an open-ended question addressing any situations perceived as unsafe; and (3) the ability to perform the procedure in a clean and sterile manner, also evaluated via an open-ended question. Between two and twelve hours after the refill at home, the researcher at the hospital will contact all patients by phone to assess the occurrence of any adverse events.

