### Health expenditure

Expenditures related to in-hospital care will be extracted from hospital claims data. All other healthcare-related costs will be gathered through telephone interviews with patients, conducted four weeks after the first and second medication refills. During these calls, researchers will ask patients whether they have had any medical consultations, hospital admissions, adverse events, changes in medication, or incurred any additional healthcare costs.

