## **Study Design**

### Study Design and patient enrollment

The IMPROVE study is a randomized, controlled, cross-over trial to evaluate if intrathecal pump refills at home (Intervention) are better for patient comfort (Outcome) compared to intrathecal pump refills at the hospital (Control) in patients who receive IDD (Population). We will include at least 82 patients, who will each receive two refills in the outpatient clinic and two refills at home.

The physician will briefly explain the IMPROVE study to eligible patients. If the patient is interested, the researcher will explain the study concept and practical aspects of their potential participation. Additionally, the patients will be screened based on in- and exclusion criteria.

The researcher will explain the study to the patient, what's expected for them and what's in it for them. If the patient is positive about participation, IC and contact information will be provided. IC will be obtained on paper. After receiving a signed IC, the IC will be scanned and stored electronically after which the original paper version will be destroyed.

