## Immediate reporting

The percentage of patients reporting an SAE possibly related to the treatment and the total number of SAEs reported will be systematically recorded from baseline assessment until the end of the study. All SAEs will be reported to the Competent Authorities (CA) and Ethics Committee within 24 hours.

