## Tables and Figures

| What? | Patient comfort *                                                                                                                                                    | QoL *        | Pain Intensity * | Pain interference * | Stress *          | Anxiety * | Self-efficacy * | Burden caregivers * | Patient satisfaction | Tele-monitoring quality** + time | Safety                                                    | Health expenditure *** | Patient preference    |
|-------|----------------------------------------------------------------------------------------------------------------------------------------------------------------------|--------------|------------------|---------------------|-------------------|-----------|-----------------|---------------------|----------------------|----------------------------------|-----------------------------------------------------------|------------------------|-----------------------|
| How?  | GCQ                                                                                                                                                                  | MQOL + EQ-5D | VAS              | PROMIS              | Sarsted t AG & Co | STAI      | GSE             | ZBI                 | Likert-scales        | Likert-scales + time expenditure | Overall safety + environmental safety + sterile procedure | Phone calls            | Multiple choice + DCE |
| When? | At baseline * and after each intrathecal pump refill (** only applicable for refills at home)
***Four weeks after first refill and four weeks after second refill |              |                  |                     |                   |           |                 |                     |                      |                                  |                                                           |                        | After last refill     |
| Who?  | Patient                                                                                                                                                              | Patient      | Patient          | Patient             | Salivary sample   | Patient   | Patient         | Caregiver           | Patient              | Researchers                      | Patient + researchers                                     | Patient                | Patient               |

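### Adverse events are to be reported to the end of the study, but no active query about them is described after the day of the fourth refill

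*Protocol*

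**What the plan says.** Section 10.1.1 (Reporting period) states that "the total number of AEs will be systematically reported from baseline until the end of the study". Section 10.1.2 (Immediate reporting) says of serious events that they "will be systematically recorded from baseline assessment until the end of the study". Section 6.2 makes the between-location difference in these events a secondary objective, in the words "number of (serious) adverse events (e.g., infection, overdose". The end of the study is not defined for an individual patient; Section 7.4 gives only the calendar range of data collection, to 1 October 2028.

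The contacts that ask about events are these:

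- Section 6.3.2 (Safety): "Between two and twelve hours after the refill at home, the researcher at the hospital will contact all patients by phone". No matching call is described for hospital refills.
- Section 6.3.2 (Health expenditure): telephone interviews, which include adverse events and admissions, "conducted four weeks after the first and second medication refills". Section 6.3 gives the same timing, and so does the note to Table 1: "Four weeks after first refill and four weeks after second refill".

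After the fourth refill the text adds only the preference question and the discrete choice experiment to the usual assessments at the visit.

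**The concern.** The reporting promise and the contact schedule do not match. A team that followed the schedule exactly would ask nobody about events arising in the days and weeks after the last refill. Infection, which the objective names, is an event that may appear after the day of the procedure (the protocol gives no onset time).

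What is at stake is the completeness of the safety counts. The trial is meant to support moving refills into the home, and a low event count is reassuring only if someone looked for events. After the fourth refill, the described schedule stops looking on the day of the procedure.

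**Working it through.** The protocol states no figure to reproduce here. The check consists of laying out the contacts and then counting the refills affected.

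**Active queries about events, by refill**

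| Refill | Call at 2–12 h | Four-week interview | Later study visit |
|---|---|---|---|
| 1 | home only | yes | refill 2 |
| 2 | home only | yes | refill 3 |
| 3 | home only | no | refill 4 |
| 4 | home only | no | none described |

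Sources: Section 6.3.2 (Safety; Health expenditure), Section 6.3 and Table 1. Section 10.4.3 puts refills about 2–3 months apart, so a later study visit gives an opportunity to learn of events after refills 1 to 3. It is only an opportunity. The safety questions at a visit (Sections 6.3.2 and 9.2) are ratings of the procedure just performed, completed straight afterwards, and no passage describes a question about events since the previous refill. Refill 3 is therefore also thinly covered, but refill 4 is the only one with neither an interview nor a later study visit.

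**Share of refills affected**

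Inputs: at least 82 patients with four refills each (Section 7.1: "We will include at least 82 patients, who will each receive two refills in the outpatient clinic and two refills at home"), and 20% loss to follow-up over the four refills (Section 11.3).

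- No loss: 82 × 4 = 328 refills, of which 82 are fourth refills; 82 / 328 = 25.0%.
- With 20% loss: 0.8 × 82 = 65.6, so about 66 patients reach the fourth refill. The share depends on when patients leave:
  - all just before refill 4: 65.6 / (3 × 82 + 65.6) = 65.6 / 311.6 = 21.1%
  - evenly before refills 2, 3 and 4: 65.6 / 295.2 = 22.2%
  - all before refill 1: 65.6 / (4 × 65.6) = 25.0%

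The range is about 21% to 25%.

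**Split by location**

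Section 7.2 pairs one home and one clinic refill, which gives four tracks. With H for home and C for clinic these are HC-HC, HC-CH, CH-HC and CH-CH. The fourth refill is C, H, C, H, so half are at home. If the tracks are equally filled, that is about 41 in each location without loss, or about 33 in each with 20% loss.

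**The case against.** The strongest reply is that events after the fourth refill are not beyond reach. The eCRF has pages for serious and non-serious events (Section 11.4). Serious events, which include any admission, must be reported within 24 hours (Section 10.1.2). Hospital claims data are extracted (Section 6.3.2). Patients remain with their treating physician and go on needing refills. The item headed as the schedule of activities (Section 9.1) is a figure that is not shown, and it could carry a further contact.

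Much of this stands. It would be wrong to say that these events go uncollected or have no way into the database. But each of these routes is passive: someone has to volunteer the event or happen to notice it. Claims data are gathered for costs, and the within-trial economic analysis stops before the third refill, so the document does not say that claims are read for the weeks after the fourth. Future routine refills are not described as a point at which study events are asked about. The flowchart's caption mentions only the four refills, and neither the text nor Table 1 lists anything later, but the missing figure is a real limit on certainty.

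Two stronger readings are tempting and not supported:

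- A reader might infer that event counts or rates are understated by a quarter. That needs complete capture after refills 1 to 3 and none after refill 4, and the document supports neither. The protocol also plans counts of events and a percentage of patients with serious events, not a rate per refill.
- A reader might infer that the gap favours home refills. Fourth refills split about equally between locations, so the loss of delayed events is roughly balanced. The home-only call at 2–12 hours is a separate asymmetry and concerns same-day events.

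**Conclusion.** The point holds as a mismatch between a promise of systematic reporting to an undefined end of study and a contact schedule with no described active query after the day of the fourth refill. It affects about 21% to 25% of refills, on the planned 82 patients and 20% loss. Counts of delayed events are likely to be too low in both locations, to an extent that the document does not allow one to calculate. The comparison between locations should be little distorted if the tracks are equally filled and passive reporting works equally well after home and hospital refills; the absolute counts are what suffer. The conclusion rests on the text and Table 1 and would change if the flowchart shows a later contact. The matter is worth correcting because it bears on a stated objective and is cheap to fix, but it does not touch the primary outcome.

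**What to change.** Define each patient's end of safety follow-up as a fixed contact after the fourth refill, with the same timing and the same adverse-event questions for home and hospital. Two ways are open:

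- extend the existing four-week telephone interview to refills 3 and 4; or
- ask about events, and record the answer, at the patient's next routine refill.

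Then bring the reporting period in Section 10.1.1 and Table 1 into line, and the flowchart if needed.

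The cost is a protocol amendment and slightly longer participation. The calls number from about 66 (one after refill 4 for the 0.8 × 82 who reach it) to 164 (2 × 82, refills 3 and 4 without loss), made by the existing researchers with an existing script. The alternative costs one recorded question per patient at a visit that takes place anyway, with a longer wait of about 2–3 months.

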## Relationship to treatment

The steering committee will determine the relationship to the treatment:

- **Definitely related:** There is clear evidence to suggest a causal relationship, and other possible contributing factors can be ruled out. The clinical event, including an abnormal laboratory test result, occurs in a plausible time relationship to the study intervention and cannot be explained by concurrent disease or other drugs or chemicals.
- **Probably related:** There is evidence to suggest a causal relationship, and the influence of other factors is unlikely. The clinical event, including an abnormal laboratory test result, occurs within a reasonable time after administration of the study intervention, is unlikely to be attributed to concurrent disease or other drugs or chemicals.
- **Potentially related:** There is some evidence to suggest a causal relationship (e.g., the event occurred within a reasonable time after administration of the study intervention). However, other factors may have contributed to the event (e.g., the participant's clinical condition, other concomitant events). Although an AE may rate only as "possibly related" soon after discovery, it can be flagged as requiring more information and later be upgraded to "probably related" or "definitely related", as appropriate.
- **Unlikely to be related:** A clinical event, including an abnormal laboratory test result, whose temporal relationship to the study intervention makes a causal relationship improbable (e.g., the event did not occur within a reasonable time after administration of the study intervention) and in which other drugs or chemicals or underlying disease provides plausible explanations (e.g., the participant's clinical condition, other concomitant treatments).
- **Not related:** The AE is completely independent of the study intervention, and/or evidence exists that the event is definitely related to another etiology. There must be an alternative, definitive etiology documented by the clinician.

### *Serious adverse event or reaction*

## Definition

A serious adverse event or serious adverse reaction is defined as any untoward medical occurrence or response to a medicinal product or treatment that at any dose:

- Results in death
- Is life-threateninga
- Results in patient hospitalization
- Results in a persistent or significant disability/incapacity
- Results in congenital anomalies/birth defects
- Important adverse events that are not immediately life-threatening or do not result in death or hospitalization but may jeopardize the patient or may require intervention to prevent one of the outcomes listed.

aThe term "life threatening" in the definition of SAE refers to an event in which the subject was at risk of death at the time of the event. It does not refer to an event which hypothetically might have caused death if it was more severe.

## Immediate reporting

The percentage of patients reporting an SAE possibly related to the treatment and the total number of SAEs reported will be systematically recorded from baseline assessment until the end of the study. All SAEs will be reported to the Competent Authorities (CA) and Ethics Committee within 24 hours.

## *Suspected unexpected serious adverse reaction (SUSAR)*

### Definition

A SUSAR is defined as a serious adverse reaction that occurs in a clinical trial participant, which is assessed as being suspected as well as unexpected, and which is having a reasonable possibility of having a causal relationship with the study medication.

### Reporting

All SUSARs must be reported to the ethics committee and health authority as per EU (European Union) and Belgian legislation. The reporting period for SUSARs if fatal or life-threatening is as soon but not later than 7 days after becoming aware. For SUSARs not fatal or non-life threatening the reporting period is 15 days after becoming aware. The sponsor will report to the Ethics Committee and Health Authorities.

## *Procedures for handling special situations*

### Overdose and pocket refill management

Following the refill, a post-refill evaluation using an ultrasound device (Clarius C3 Scanner, Vancouver, Canada) will be performed to confirm that the pump was correctly refilled and that no subcutaneous drug injection occurred. If a pocket refill or symptoms of overdose are detected, an emergency procedure will be initiated.

### **Morphine**

#### Symptoms:

- Respiratory failure
- Profound drowsiness or unresponsiveness
- Seizures
- Coma or loss of consciousness
- Bradycardia

If any of these symptoms occur, immediate medical intervention is essential. 112 will be called, it will be ensured that the airway remains clear, followed by placing the patient in a safe position.

### **Baclofen**

#### Symptoms:

- Hypotonia or flaccid paralysis
- Decreased level of consciousness of coma
- Respiratory depression
- Hypotension
- Nausea and vomiting
- Seizures

In the event of suspected intrathecal baclofen overdose, immediate medical intervention is critical. 112 will be called, it will be ensured that the airway remains clear, followed by placing the patient in a safe position.

### Data Collection

An Electronic Data Capture system “REDCap (Research electronic Data Capture)” will be used for data collection. The system is validated and access to all levels will be granted/revoked by the sponsor representative. Trial data should be entered within a reasonable time after the subject attended the visit. Corrections/modifications will be automatically tracked by an audit trail detailing the date and time of the correction and the name of the person performing the correction. Data will be collected through online self-reported questionnaires. Participants will be provided with a tablet with a link to

the relevant questionnaires. For participants who are unable to complete the questionnaires online, or in cases where internet connectivity is limited, paper-based versions of the questionnaires will be available.

IC will be obtained from all participants before the initiation of the study. This consent constitutes the legal basis for the collection, processing, and management of personal data in compliance with applicable data protection regulations.

To support participant retention and ensure completion of study procedures, patients will receive a reminder of their upcoming refill appointment. Following each refill, they will be given a tablet with the relevant questionnaires.

#### Database Management and Quality Control

During the research, data management and storage will be overseen by the pre-doctoral investigators. All collected information will be saved on a dedicated, system-encrypted Pixiu or SharePoint site at Vrije Universiteit Brussel, with access restricted to the investigators and supervisors. A secure external hard drive will serve as an additional backup. Once the study concludes, responsibility for the data will transfer to the principal investigator, and all files will be migrated to the Vrije Universiteit Brussel Archive for a 25-year retention period. Prior to archiving, any direct personal identifiers will be permanently removed.

Personal data will be processed in accordance with the applicable EU regulations, including the General Data Protection Regulation (GDPR), the Belgian Law of 30 July 2018 on the protection of personal data, and in compliance with Good Clinical Practice (GCP) guidelines. Pseudonymization will be performed as soon as data collection starts. As an additional safety measure, the file linking the pseudonymization with the original direct identifiers will be encrypted before uploading it on Pixiu/SharePoint.

Specific measures will be implemented to prevent unauthorized access, as personally identifiable data will be collected. REDCap will be used for data collection. To enhance data protection, responses to the questionnaires will only be accessible to the study team. Collected data will be protected by a password. Additionally, personally identifiable information and clinical trial data will be stored separately, with the last one linked only to a unique participant ID. Access to ICs, personally identifiable data and the linkage between identifiers and participant ID will be restricted to the investigators and supervisors and will be stored separately from the clinical trial data.

Vrije Universiteit Brussel adheres to the FOSB metadata standard, developed by the Flemish Open Science Board, which is compatible with the international DataCite metadata schema. At the project level, essential metadata—including the project title, investigators, objectives, hypotheses, funding information, study protocol, sampling procedures, data collection instruments, and technical infrastructure (hardware and software)—will be documented and made available through research plans and publications. At the database level, an inventory of the data files will be provided via a comprehensive read-me file. At the data level, a codebook will accompany the dataset, outlining the structure and meaning of quantitative variables, along with the scripts used for data analysis.

Personal data will be processed in accordance with the EU's Data Protection Directive (Directive 95/46/EC) and regulation EC45/2001, the relevant Belgian legislation concerning data protection of July 30th, 2018, and GCP. As we collect personal identifiable data, the following steps are taken to limit unauthorized access. ICs will be preserved at a secure location at the VUB. REDCap will be used for data collection to improve data protection as responses to questionnaires will only be accessible to the study team. Collected data will be password protected. Personal identifiable and clinical trial data will be separated, with the latter receiving a unique participant ID. Access to ICs, personal identifiable data and the link with the participant ID will be restricted to the investigators and supervisors and stored separately from the trial data. Eventual further dissemination of data will only occur in a pseudonymized or aggregated way.

